### Groups and sample size

The necessary sample size was estimated to be 99 based on a preliminary trial with a small sample size. During the preliminary phase, eighteen participants were included and randomly divided into 3 groups of 6. According to the protocol, differences in UCSS between week 8 and the baseline value were detected. The mean ± standard deviation of UCSS reduction was obtained at week 8 and week 0 individually: 0.33±0.817, −0.80±0.837, −1.0±1.000. The standard deviation was 0.873, and PASS 11 software was used to estimate the sample size by means of the following formula:

$$ 1-\beta =1- probF\;\left[{F}_{1-a,G-1,N-G,}\;\left(G-1\right),N-G, NV/{\sigma}^2\right] $$

The significance level, *α*, was set to 0.05; the power of a test, 1 − *β*, was 0.80; the number of groups, *G*, was 3; *N* represents the sample size; *V* represents the variance of the group averages, $$ V=\Sigma \left({\left({\mu}_i-\overline{\mu}\right)}^2\right)/G $$; σ represents the standard deviation.

A total of 126 participants will be included to allow for 20% loss to follow-up. There will be 3 groups:
Control group: (*n*=42) These individuals will receive micro-arthroscopic surgical procedures twice (day 0 and 4th week), and 0.9% saline will be administered instead of PS.PDT once group: (*n*= 42) Participants will receive PDT on day 0, followed by 0.9% saline administration instead of PS in the 4th week.PDT twice group: (*n*=42) Individuals will receive PDT twice: once on day 0 and once in the 4th week.

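### The planning SD of 0.873 is not the pooled SD of the pilot as described (0.888); its source is unstated, and the effect on the sample size is small and depends on the sign of the control mean

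*Protocol article*

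**What the plan says.** All of this stands in the protocol article under Groups and sample size. "The necessary sample size was estimated to be 99 based on a preliminary trial with a small sample size". In that preliminary phase "eighteen participants were included and randomly divided into 3 groups of 6", and the changes in UCSS between baseline and week 8 are printed as "0.33±0.817, −0.80±0.837, −1.0±1.000". The planning SD follows: "The standard deviation was 0.873, and PASS 11 software was used to estimate the sample size".

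The calculation is a one-way ANOVA F test with three groups, two-sided by nature, at alpha 0.05 and power 0.80. Its noncentrality is N·V/σ², where V is the variance of the group means. The 99 is raised to 126 (42 per arm) for 20% loss. The Statistical analysis section plans the same one-way ANOVA for the primary outcome.

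The article does not say how 0.873 was obtained, how many patients were analysed in each pilot group, or which printed result belongs to which arm. The arm order used below (control, PDT once, PDT twice) is taken from the order in which the protocol lists its groups.

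**The concern.** The SD enters the sample-size formula directly, and the article prints everything a reader should need to check it. When group sizes are equal, the pooled SD depends only on the three group SDs, and here it does not come to 0.873. Either the planning SD was taken from something other than the pilot as described, or the pilot is described incorrectly. In the first case the required sample size shifts a little. In the second, fewer than 18 patients stand behind the planning figures and the reader should be told so.

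**Working it through.** **Inputs.** From Groups and sample size: pilot SDs 0.817, 0.837, 1.000; pilot means +0.33, −0.80, −1.0; planning SD 0.873; alpha 0.05; power 0.80; three groups; 99 evaluable; 126 enrolled; 20% loss.

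**1. Pooled SD for equal groups.**
sqrt((0.817² + 0.837² + 1.000²)/3) = sqrt((0.6675 + 0.7006 + 1.0000)/3) = sqrt(0.7894) = 0.888.
Letting each printed SD vary within its rounding gives 0.8880 to 0.8890. The simple average of the SDs is 0.885. Neither is 0.873.

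**2. Can unequal numbers give 0.873?** Weighting by degrees of freedom:
- 6/5/4: sqrt((5×0.6675 + 4×0.7006 + 3×1.0000)/12) = sqrt(9.1397/12) = 0.8727, which rounds to 0.873.
- 4/4/3: sqrt((3×0.6675 + 3×0.7006 + 2×1.0000)/8) = 0.8735. Within rounding of the printed SDs this runs from 0.8730 to 0.8740, so it also reaches 0.873.

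A search over 2 to 6 patients per group, allowing for rounding, finds these two and no others.

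**3. Do the means fit six patients?** This assumes that UCSS changes come in whole or half points; the article does not state the step.
- Six whole-point changes can average −0.67 or −0.83, and six half-point changes −0.75 or −0.83. None rounds to −0.80, so −0.80±0.837 does not fit n = 6. It fits n = 5.
- +0.33±0.817 fits n = 6.
- −1.0±1.000 on whole points fits n = 3 or 5, but not 4 or 6. On half points it fits 3, 4, 5 or 6.

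So 6/5/4 works on half points but not on whole points. On whole points the candidates are 6/5/5, which pools to 0.883, and 6/5/3, which pools to 0.860. Neither is 0.873.

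**4. The plan's own 99.** Using the article's formula, with V = Σ(μᵢ − mean)²/3 and the smallest equal-group N with power of at least 0.80:

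| First mean | V | SD | Smallest N | Power at that N | Power at 99 |
|---|---|---|---|---|---|
| +0.33 (as printed) | (0.82² + 0.31² + 0.51²)/3 = 0.3429 | 0.873 | 27 | 84.2% | above 99.9% |
| +0.33 (as printed) | 0.3429 | 0.888 | 27 | 82.8% | above 99.9% |
| −0.33 | (0.38² + 0.09² + 0.29²)/3 = 0.0789 | 0.873 | 99 | 81.2% | 81.2% |
| −0.33 | 0.0789 | 0.888 | 102 | 81.1% | 79.8% |

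With −0.33 and SD 0.873, N = 96 gives 79.9%, so 99 is exactly the smallest equal-group total. The printed signs do not reproduce 99. Giving all three means the same sign does; any other sign pattern spreads the means at least as far as the printed one and needs no more than 27.

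**5. Allowance for loss.** 33/0.8 = 41.25, rounded up to 42 per arm, or 126, so the article's step is correct. With SD 0.888 and the −0.33 reading, 126 × 0.8 = 100.8 evaluable gives power of about 80.6%. A requirement of 102 evaluable out of 126 is 102/126 = 0.81, which allows 19% loss.

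**The case against.** The wording about groups of 6 describes how patients were allocated, not how many were analysed, and the article never calls 0.873 a pooled SD of all 18. An SD from fewer patients would then not strictly contradict it. That is fair, and it is why this point does not call 0.873 wrong outright. What stands is that the figure cannot be obtained from the pilot as described and that no other source is given.

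The difference is also trivial beside the pilot's imprecision. An SD of 0.888 on 15 degrees of freedom has a 95% interval of about 0.66 to 1.37 if changes are normal, and the discrepancy is 0.015. This stands too: the point is about a traceable input, not a materially underpowered trial. The mismatch between the printed +0.33 and the stated 99 is the larger fault in the same paragraph.

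Three stronger readings are tempting and are not supported:
- **Only 6/5/4 fits, so three of 18 pilot patients were lost, all in the PDT arms.** The SDs alone also admit 4/4/3 within rounding, and 6/5/4 fails in the third group if scores are whole points. The article reports no losses and does not label the results by arm. Neither concealed nor arm-dependent loss is shown.
- **The sample size is too small.** With the printed means, 99 is far more than the 27 required. A shortfall appears only if the control mean is −0.33 and all six patients per arm were analysed.
- **Both at once.** They exclude each other. If 6/5/4 were analysed, 0.873 is the right pooled SD and 99 stands on the −0.33 reading. If 6/6/6 were analysed, the SD is 0.888 and there were no losses.

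A requirement of 129 enrolled can also be derived (34/0.8 = 42.5, rounded up to 43 per arm). It comes only from rounding up to equal groups at the full 20% loss, since 126 with that loss still meets 80% power.

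**Conclusion.** The point holds in a limited form. The planning SD of 0.873 does not match three pilot groups of 6 with the printed SDs, which pool to 0.888, and this does not depend on rounding. It is plausible that fewer than six patients stand behind at least one pilot result, but that inference assumes whole- or half-point scores, and the number and arm of any missing patients are not shown.

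The size is small: three more evaluable patients (102 instead of 99), or 1.4 percentage points of power at 99 (81.2% to 79.8%). Even this rests on two assumptions: that the control mean is −0.33, which is not what is printed, and that all 18 were analysed. With the printed means the SD makes no difference to the required total. The documents do not show whether the sign in the text or the value entered in the software is at fault.

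**What to change.** In Groups and sample size, state the control mean with its sign, label the three pilot results by arm, give the number analysed in each arm and say where 0.873 comes from. Then rerun the calculation from those inputs.

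- If all six per arm were analysed and the control mean is −0.33, replace 0.873 with 0.888. Then either restate the evaluable requirement as 102 (34 per arm), with 126 enrolled allowing 19% loss, or keep 99 and restate its power as 79.8%.
- If fewer were analysed, correct the description of the pilot and keep 0.873, provided the numbers given reproduce it.
- If the control mean really is +0.33, the SD question does not affect the total. The 99 then needs a different justification, because those inputs give 27.

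The cost is a reworded paragraph and one rerun of the software. No extra enrolment is needed.

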### Randomization and blinding

We will recruit participants from our hospital, clinic, and by referral from other hospitals. To participate, all candidates must sign an informed consent form before entering the screening period. After the baseline survey, all identified participants will be randomly assigned to the 3 groups as previously stated. The block randomization method will be used for 1:1:1 randomization to ensure a balanced distribution between 3 groups. The random numbers will be generated using SAS 9.12 software. On this basis, randomization will be conducted by a professional nurse at the hospital follow-up center.

The researchers responsible for evaluations, application of the treatment protocol, and statistical analysis will be blinded to the group allocation of participants. The participants will also be blinded to group allocation. All researchers and patients in this trial will be informed not to communicate regarding the details of the groups. There is no difference in the appearance of PS solution and saline, enabling the double blinding to be maintained. PS or saline will be prepared by the professional nurse at the follow-up center, according to the random grouping table. Participants will be unblinded at the termination of this trial.

If emergency unblinding is deemed necessary, for example, if there is a serious adverse event (SAE) such as instrument fracture in the articular cavity, tissue hematoma, infection, or structural damage, researchers should determine the relevance of the event based on the grouping information. Effective treatment will be administered to those participants.

### Intervention

All patients will receive steroids, nonsteroidal anti-inflammatory drugs, and/or DMARDs (e.g., conventional synthetic DMARDs, biologic DMARDs, and targeted synthetic DMARDs) in accordance with the treatment guidelines.

Participants in the PDT treatment groups will be injected with a PS (aminolevulinic acid, 236 mg, dissolved in 0.9% saline to 5 mL) in the articular cavity of the knee before the operation. Participants in the control group will be injected with 5 mL of 0.9% saline instead of PS. Local anesthesia will be performed 2 h later after joint injection. Then, arthroscopy-guided minimally invasive needle-knife arthroscopy for single-hole exploration and articular cavity lavage will be performed. Pathological biopsies of the synovial tissue will be taken before laser irradiation. A laser optical fiber will be inserted into the articular cavity through a cannula. Then, with the knee joint half bent, three sites will receive laser irradiation for a total of 20 minutes: the posterior patella for 10 min and the medial and lateral condyles of the femur for 5 min each. The following parameters will be used for the laser: wavelength, 630 nm; power, 150 mW. A second operation will be performed at the 4th week. Further details are shown in Fig. 2.

**Fig. 2 Fig2:**
[figure not shown]
Photodynamic therapy process and scenarios

### Evaluation procedure

The researchers will record participants’ postoperative improvement and general condition, including body temperature and respiration, pulse, and heart rate, during face-to-face follow-up visits. The items evaluated during each follow-up visit are shown in Table 2. All the data will be uploaded to the case report form (CRF) by rigorously trained data collectors. To reduce the rate of loss to follow-up, we will also communicate with participants by a variety of methods, including WeChat, telephone, text message, and e-mail, to remind them to return for further examination.

**Table 2 Tab2:** Follow-up plan

***Follow-up time***	***Evaluation index***
*Baseline*	*UCSS, clinical evaluation of knee joints, DAS28, antibody levels, inflammation indicators, X-ray, routine blood test, routine urine test, blood biochemical test, infectious disease screening*
*W0* *(first operation)*	*Pathological biopsies of synovial tissue*
*W4±3 d* *(second operation)*	*UCSS, clinical evaluation of knee joints, DAS28, antibody levels, inflammation indicators, pathological biopsies of synovial tissue*
*W8±3 d*	*UCSS, clinical evaluation of knee joints, DAS28, antibody levels, inflammation indicators, blood biochemical test*
*W24±5 d*	*UCSS, clinical evaluation of knee joints, DAS28, antibody levels, inflammation indicators*
*W48±5 d*	*UCSS, clinical evaluation of knee joints, DAS28, antibody levels, inflammation indicators, X-ray*

*W* week, *d* days

### Outcome and safety measures

#### Outcome measures

Primary outcome measure

The Ultrasound Compound Score of Synovitis (UCSS) will be calculated according to the EULAR-OMERACT combined scoring system for grading synovitis in rheumatoid arthritis [11]. Improvement in the UCSS compared with the control group will be the primary endpoint.
(2)Secondary outcome measures
Clinical evaluation of knee joints: The circumference will be measured 2 cm above the upper edge of the patella, and joint flexion and extension will be measured to assess the range of motion.DAS28-ESR: DAS28-ESR= 0.56 × the total number of tender joints + 0.28 × the total number of swollen joints + 0.70 × ln(ESR) + 0.014 × general health assessment score.Antibody levels: Serum will be collected by centrifugation, and then the RF and anti-CCP antibodies will be detected by a standard commercially available test kit.Inflammation indicators: Serum will be obtained by centrifugation, and then ESR and CRP will be detected by standard commercially available test kits.X-ray: X-rays of the knee joint will be used to evaluate bone destruction.Pathological biopsies of synovial tissue: The synovium of the joint, which will be acquired before laser irradiation during each operation, will be fixed, embedded by dehydration, and sectioned. The synovium will be stained with hematoxylin and eosin for histological evaluation, and synovial histopathology will be observed, including synovial cell proliferation, inflammatory cell infiltration, and angiogenesis (pannus formation). The pathological biopsy of synovial tissue will strictly follow the clinical diagnostic protocol. The research nurses will collect specimens with special specimen boxes, record basic information on the subjects, and then send specimens to the pathology department for testing and preservation as soon as possible.

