**Methods and analysis:**

This protocol is for a single-center, randomized, double-blind, blank-controlled prospective trial. A sample of 126 RRA patients will be randomly divided into 3 groups: the control group, the “PDT once” group, and the “PDT twice” group, with 42 participants per group. The trial will be conducted by the Rheumatology and Immunology Department of the Integrated Hospital of Traditional Chinese Medicine, Southern Medical University. The Ultrasound Compound Score of Synovitis (UCSS) has been selected as the primary outcome measure. The secondary outcome measures include knee joint clinical assessments, ratio of relapse, duration of remission, Disease Activity Score in 28 joints (DAS28), inflammation indexes, serum concentrations of specific antibodies, and changes in articular structures as detected by X-ray scans in the 48th week. The improvement ratios of the UCSS at the 8th, 24th, and 48th weeks (compared with baseline) reflect short-, medium-, and long-term time frames, respectively.

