#### The inclusion and exclusion criteria

The inclusion and exclusion criteria for the patients are presented in Table 1.

**Table 1 Tab1:** Inclusion and exclusion criteria

*Inclusion criteria*	
*1. Male or female patients aged between 18 and 70 years* *2. Patients who meet the diagnostic criteria for RRA* *3. Patients with swelling of at least one knee for 1 month* *4. Patients with synovial hyperplasia confirmed by ultrasound or MRI: UCSS ≥ 2 points and/or single-site MR scores ≥2 points* *5. Patients who are capable of signing informed consent and completing the trial as required* *6. Patients who have good compliance and will complete follow-up*	
*Exclusion criteria*	
*1. Patients with severe primary diseases, such as disorders of the cardiovascular system, liver, kidneys, brain, or hematopoietic system* *2. Patients with infections or coagulation abnormalities* *3. Breastfeeding or pregnant women* *4. Patients who are allergic to anesthetics or PSs* *5. Patients who have undergone intra-articular drugs injection within the past month* *6. Patients with arthritic knee joints that show osteotropic ankylosis on X-ray examination*	

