#### Statistical analysis

SPSS 20.0 statistical software will be used to analyze the measurement data, described as the means ± standard deviations ($$ \overline{x}\pm s $$), and the main evaluation index (improvement in the UCSS compared with the baseline value) will be analyzed by single-factor variance analysis among the three groups. ANOVA will be used for repeated measurement data of the secondary evaluation indicators to explore the principal and interactive effects of grouping and time. Multiple paired *t*-tests comparing two time points (before and after treatment) will be used to analyze repeated measurements. Single-factor ANOVA will be used to compare the differences at the same time points after treatment between the three groups. Differences will be statistically significant at *P* <0.05.

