### Strengths and limitations of this study

The aim of this trial is to evaluate the short-, medium-, and long-term clinical efficacy of PDT in the treatment of RRA synovial hyperplasia and synovitis with a 1-year follow-up.An improvement in the UCSS value compared with the baseline will be the primary endpoint based on the EULAR-OMERACT combined scoring system for grading synovitis in RRA.PDT has the advantages of minimal trauma, stronger targeting, fewer side effects, and definite curative effects, which makes it more acceptable to patients than steroid injections or arthroscopic synovectomy.The trial will take place at only a single center.

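### The primary endpoint has no single metric or time point: the abstract points to UCSS improvement ratios at three visits, the sample size to the absolute change at week 8

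*Protocol article*

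**What the plan says.** Five places in the protocol article bear on the primary endpoint.

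- **Abstract, Methods and analysis.** UCSS is named as the primary measure. "The improvement ratios of the UCSS at the 8th, 24th, and 48th weeks (compared with baseline" are then said to stand for the short-, medium- and long-term results.
- **Groups and sample size.** In the preliminary phase "differences in UCSS between week 8 and the baseline value were detected". The group means and SD of that difference feed the sample size of 99, raised to 126 for loss to follow-up.
- **Outcome measures.** "Improvement in the UCSS compared with the control group will be the primary endpoint".
- **Statistical analysis.** "the main evaluation index (improvement in the UCSS compared with the baseline value) will be analyzed by single-factor variance analysis among the three groups". Later in the same paragraph: "Single-factor ANOVA will be used to compare the differences at the same time points after treatment between the three groups". The only threshold is "Differences will be statistically significant at *P* <0.05".
- **Strengths and limitations of this study.** "An improvement in the UCSS value compared with the baseline will be the primary endpoint".

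Table 2 (Evaluation procedure) schedules UCSS at baseline and at weeks 4, 8, 24 and 48.

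**The concern.** A primary endpoint needs a variable, a scale and a time. The section written to define it gives only the variable. The two sections that add detail disagree: one has a ratio at three weeks, the other an absolute difference at one week.

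Two things are at stake. First, with four post-baseline UCSS visits, two possible scales and one unqualified threshold, the result called primary could be settled after the data are seen, and its error rate would then exceed 5%. Second, the planned size supports only one of the candidate endpoints. A primary result on the ratio, or at week 24 or 48, would rest on a quantity for which the protocol has no planning figures.

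**Working it through.** **1. The places side by side**

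| Place | Scale | Week | Comparison |
|---|---|---|---|
| Abstract | ratio | 8, 24, 48 | with baseline |
| Groups and sample size | absolute difference | 8 | three groups (F test) |
| Outcome measures | not stated | not stated | with control |
| Statistical analysis | not stated | not stated | with baseline, among three groups |
| Strengths and limitations | not stated | not stated | with baseline |

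The last column is not a conflict. Change from baseline is the variable, and the groups are compared on it. The scale and week columns cannot be reconciled in the same way.

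**2. What the planned size covers**

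Inputs from Groups and sample size: means 0.33, −0.80 and −1.0; SD 0.873; G = 3; α = 0.05; power 0.80. The formula is the power of a one-way F test with noncentrality λ = N·V/σ², where V = Σ(μᵢ − μ̄)²/G.

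- Means as printed: μ̄ = −0.49 and V = (0.82² + 0.31² + 0.51²)/3 = 0.343. This needs 9 per group, or 27, not 99.
- First mean taken as −0.33 (an assumption): μ̄ = −0.71 and V = (0.38² + 0.09² + 0.29²)/3 = 0.0789. At N = 99, λ = 99 × 0.0789/0.762 ≈ 10.2 and power is 81%. This needs 33 per group, or 99. Then 33/0.8 = 41.25, rounded up to 42 per group, or 126.

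The sign of the first mean is a separate matter. Under either sign the inputs are week-8 differences, and the calculation is for one test at 0.05. No mean or SD is given for weeks 24 or 48, or for a ratio.

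**3. The two scales differ**

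The abstract's ratio is not defined; I take it as change relative to baseline. A one-point fall is then 1/2 = 50% from a baseline of 2 but 1/3 = 33% from a baseline of 3. Patients with the same absolute change get different ratios, so the two analyses can disagree.

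**4. Error rate if any of the three weeks could count**

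With independent visits: 1 − 0.95³ = 14.3%.

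With correlated visits, by simulation of three one-way F tests at 0.05 with no true effect (normal outcomes, equal correlation between visits, 40,000 runs per setting):

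| Correlation (assumed) | 33 per group | 42 per group |
|---|---|---|
| 0 | 14.6% | 13.9% |
| 0.3 | 13.7% | 13.7% |
| 0.5 | 12.8% | 13.0% |
| 0.7 | 11.4% | 11.2% |
| 0.9 | 8.7% | 8.6% |

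The values at zero correlation differ from 14.3% only by simulation error. A free choice between ratio and difference could add to these rates; that was not quantified.

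**The case against.** The strongest reply is that a sensible reading has no problem. The trial is sized on the absolute week-8 difference. If that is the primary endpoint, there is one test on exactly the quantity planned for. The abstract only says that the three weeks reflect three time frames; it does not call each one primary or say that one success is enough. In Statistical analysis, the sentence on ANOVA at the same time points follows sentences on secondary indicators and repeated measurements, so it may not concern the primary index. The Background calls the trial a pilot study, which lowers the weight on strict error control. An article also condenses a fuller document.

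Much of this stands. A reader might infer that the plan sets up three unadjusted chances to succeed, but that is one reading and not a stated rule. A reader might also count comparisons of each PDT group with control and reach a higher error rate, but Statistical analysis names only a three-group ANOVA for the main index. Finally, the entry criterion "UCSS ≥ 2 points and/or single-site MR scores ≥2 points" might suggest that patients with little room to improve on UCSS will cost power. The protocol gives no share of such patients, and the size of any loss depends on the sign of the first pilot mean. No power loss can be derived from the document, and eligibility is a separate question.

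What does not stand is the appeal to condensing. The article has a section for the primary outcome, and its abstract and sample-size section point to different answers. That is a contradiction in the text. The week-8 reading is the most reasonable one, but no sentence adopts it.

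**Conclusion.** The point holds in this form: the protocol leaves the scale and the week of its primary endpoint open and gives conflicting indications of both. If a significant ANOVA at any of weeks 8, 24 or 48 could be reported as the primary result, the false-positive chance is roughly 8 to 14% instead of 5%. That range depends on the any-visit reading and on assumed correlations from 0.9 down to 0. Under the week-8 absolute-difference reading there is no inflation and the sizing is aimed at the right quantity. Whatever the error rate, a ratio primary or a primary at week 24 or 48 is not covered by the sample size. It should be corrected before any unblinded data are seen, because the correction is cheap and cannot be made credibly afterwards.

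**What to change.** State one primary endpoint in the same words in the abstract, Outcome measures, Statistical analysis, and Strengths and limitations: absolute change in UCSS from baseline to week 8, compared among the three groups by one-way ANOVA at 0.05. Make weeks 24 and 48 secondary, for example tested in fixed order after a significant week 8. Define the improvement ratio and report it descriptively only. Check that the registry entry says the same.

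The cost is wording and, by the protocol's own rule on modifications, ethics committee approval. Visits and measurements do not change, and this point does not require changing the 99 evaluable or 126 enrolled. The downside is that weeks 24 and 48 carry no stand-alone confirmatory claim.

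If the sponsor wants each of the three weeks to support a claim on its own, a multiplicity rule and a larger trial are needed. With Bonferroni (0.05/3 = 0.0167), the first pilot mean read as −0.33, and the week-8 effect and SD assumed to hold at all three visits, power per test at 99 evaluable falls from 81% to 67%. Restoring 80% takes 42 evaluable per group (126), and 42/0.8 = 52.5, so 53 per group or 159 enrolled.

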### Patients

#### RRA diagnostic criteria

(1) The 1987 American Rheumatism Association (ARA) classification criteria for RA are as follows: (i) morning stiffness in and around joints lasting at least 1 hour before maximal improvement; (ii) Soft tissue swelling or arthritis of 3 or more joints observed by a physician; (iii) Swelling or arthritis of the proximal interphalangeal, metacarpophalangeal, or wrist joints; (iv) Symmetric swelling (arthritis); (v) Rheumatoid nodules; (vi) The presence of rheumatoid factor; and (vii) radiographic erosions and/or periarticular osteopenia in hand and/or wrist joints. Criteria i to iv must have existed for at least 6 weeks. Rheumatoid arthritis is defined as the presence of 4 or more criteria [8]. (2) RA will be classified as RRA if low activity (Disease Activity Score in 28 joints calculated with erythrocyte sedimentation rate (DAS28-ESR)<3.2) or remission (DAS28-ESR<2.6) [9, 10] is not achieved in response to more than 3 months of regular, sufficient treatment, including traditional drugs such as nonsteroidal anti-inflammatory drugs, more than two DMARDs and/or biologic DMARDs, or combined therapy.

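### The printed DAS28-ESR formula uses raw joint counts instead of their square roots, so the score is too high once either count reaches 2 and does not fit the protocol's own cut-offs

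*Protocol article*

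**What the plan says.** Under Outcome measures, the protocol article lists DAS28-ESR as a secondary outcome and gives its formula in words: "DAS28-ESR= 0.56 × the total number of tender joints + 0.28 × the total number of swollen joints", continuing with "0.70 × ln(ESR) + 0.014 × general health assessment score". The counts enter linearly. No square root appears here or elsewhere in the article, and no other section gives a different formula.

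The RRA diagnostic criteria apply cut-offs to a score of the same name: "low activity (Disease Activity Score in 28 joints calculated with erythrocyte sedimentation rate (DAS28-ESR)<3.2) or remission (DAS28-ESR<2.6". A patient is refractory if this state "is not achieved in response to more than 3 months of regular, sufficient treatment". Inclusion criterion 2 in Table 1 then admits "Patients who meet the diagnostic criteria for RRA".

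Table 2 schedules DAS28 at baseline and at weeks 4, 8, 24 and 48. The Statistical analysis section assigns repeated-measures ANOVA to the secondary indicators.

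**The concern.** DAS28-ESR is a named index with a fixed definition, in which 0.56 and 0.28 multiply the square roots of the tender and swollen counts. The article keeps those weights and the usual cut-offs but puts raw counts in the formula, so formula and cut-offs are on different scales.

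Two uses could be affected. As a secondary outcome, the score would be inflated unevenly, more so the more joints are involved. Group means, standard deviations and changes over time would then not be comparable with DAS28 results elsewhere. As part of the entry definition, an inflated score can only err towards calling a patient refractory. Because any score under 2.6 is also under 3.2, the threshold that decides entry is in effect 3.2.

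**Working it through.** **Inputs from the protocol article:** the weights 0.56, 0.28, 0.70 and 0.014 (Outcome measures), the cut-offs 3.2 and 2.6 (RRA diagnostic criteria), and 28 joints (the name of the index). **Assumed:** the square-root definition, which the article does not print, and illustrative ESR and general health (GH) values, since the article gives no patient data. There is no stated figure to reproduce.

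**Step 1. The two forms**, with T tender and S swollen joints:

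- Printed: 0.56·T + 0.28·S + 0.70·ln(ESR) + 0.014·GH
- Square-root: 0.56·√T + 0.28·√S + 0.70·ln(ESR) + 0.014·GH

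The last two terms cancel, so the excess is 0.56(T − √T) + 0.28(S − √S), whatever the ESR and GH. It is zero when both counts are 0 or 1 and positive otherwise.

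| T / S | Excess of printed form |
|---|---|
| 0 or 1 / 2 | 0.28 × 0.586 = 0.16 (smallest) |
| 2 / 0 or 1 | 0.56 × 0.586 = 0.33 |
| 2 / 2 | 0.33 + 0.16 = 0.49 |
| 4 / 4 | 1.12 + 0.56 = 1.68 |
| 10 / 8 | 3.83 + 1.45 = 5.28 |
| 28 / 28 | 23.52 − 4.44 = 19.08 |

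**Step 2. Scale against the cut-offs.** At 28/28 with ESR 20 and GH 30, the common terms are 0.70 × ln 20 + 0.014 × 30 = 2.10 + 0.42 = 2.52. The printed score is 23.52 + 2.52 = 26.04; the square-root score is 4.44 + 2.52 = 6.96. Cut-offs of 3.2 and 2.6 are plausible on a scale that reaches about 7, not on one that reaches about 26.

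**Step 3. Effect as an outcome.** Suppose tender joints fall from 10 to 4. The printed score drops by 0.56 × 6 = 3.36. The square-root score drops by 0.56 × (3.162 − 2) = 0.65. Halving the ESR moves either score by 0.70 × ln 2 = 0.49. In the printed form, joint counts swamp the other components.

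**Step 4. Effect at the 3.2 cut-off**, if the printed form is used for screening. Example with T = S = 2, ESR 10, GH 20:

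- Printed: 1.12 + 0.56 + 1.61 + 0.28 = 3.57 (refractory)
- Square-root: 0.79 + 0.40 + 1.61 + 0.28 = 3.08 (low activity)

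Over all pairs T, S = 0 to 28, the pairs below 3.2 with square roots that the printed form puts at or above 3.2 are:

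| ESR / GH (assumed) | Pairs that cross, of those below 3.2 |
|---|---|
| 5 / 10 | 95 of 111 |
| 10 / 20 | 29 of 38 |
| 15 / 20 | 13 of 19 |
| 20 / 30 | 3 of 7 |
| 30 / 30 | 1 of 3 |
| 40 / 50 | 0 of 0 |

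These count possible combinations; they are not proportions of patients. At ESR 40 and GH 50 the common terms alone give 2.58 + 0.70 = 3.28, so no one is below 3.2 under either form and no one can cross.

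**The case against.** **The square-root form is not in the article.** True. Neither it nor a maximum score is printed, so the in-document evidence shows a poor fit, not a strict contradiction. But the article uses the name, weights and cut-offs of a standard index, and only the square-root form gives a scale on which those cut-offs make sense.

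**A symbol may have been lost in text conversion.** This cannot be fully excluded: the formula is running text, and the list around it has run together. It is unlikely, because the joint terms are written in words and the multiplication signs and ln survive on the same line.

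**The site may use a standard calculator.** Possible, and this objection limits the consequences. The RRA criteria cite their own references and do not point to the printed formula, and the CRF and analysis program are not shown. Every effect on data is therefore conditional on the formula being applied.

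**Stronger readings that a reader might infer.** One is that the cut-offs misclassify patients generally. Only patients below a cut-off on the square-root score and not on the printed one are affected, and Table 1 also requires knee swelling and imaging-confirmed hyperplasia. Another is that remission would be under-reported as an outcome. The 2.6 cut-off appears only in the entry definition, and the duration of remission named in the abstract is not tied to DAS28.

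This is not a detail that could be left to an analysis plan: the article prints a specific formula, and that formula is wrong.

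**Conclusion.** The formula is misstated and should be fixed. Taking the square-root form as the definition of DAS28-ESR, the printed score is too high for every patient with two or more tender or two or more swollen joints, by 0.16 to 19.08 points.

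If applied, it distorts a secondary outcome at all five scheduled assessments. If also applied at screening, it would over-include some patients with low ESR, low general health score and few joints, always in that direction; the article gives no data from which to say how many.

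It does not threaten the main result. The primary outcome is UCSS, the sample size was derived from UCSS reductions, and neither uses DAS28. That, and the fact that scores can be recalculated from their components, keeps this below the level of a critical defect.

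**What to change.** Restate the formula under Outcome measures as 0.56 × √(tender joints) + 0.28 × √(swollen joints) + 0.70 × ln(ESR) + 0.014 × general health, and have the RRA diagnostic criteria refer to it so that screening and outcome use one definition.

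Confirm which version the CRF and the analysis program use. If either holds the printed form, correct it and recalculate all scores from the recorded counts, ESR and general health. Re-check the eligibility of screened patients only if the printed form was used at screening.

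The cost is one line of text and, at most, one line of code plus a recalculation. No new data are needed, since the components must be collected for the score in any case.
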